## Primary Study Endpoints

**1. Microcirculatory studies** – pulse wave velocity (PWV), iontophoresis of acetyl choline (AcH) and sodium nitroprusside (SNip), skin autofluoresence (AF) and side stream dark field imaging of the sub lingual microcirculation.

Pulse wave velocity – we expect PWV to decrease after vitamin D therapy.

Iontophoresis – we expect lower skin micro-vessel resistance as measured by laser Doppler Flowmetry (LDF) after vitamin D therapy.

Skin autofluorescence – we expect lower deposition of advanced glycation end products after vitamin D therapy.

Sublingual microvascular flow using sidestream darkfield (SDF) imaging – we expect enhanced flow in patients treated with vitamin D

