# Study Procedures and Schedule of Assessments

Patients will be examined and assessed by an investigator at the renal outpatient department of the Royal London Hospital. Cardiac MRI will take place at the London Chest Hospital (aprox 20 min walk from RLH)

All assessments will be similar between the two groups. At each study point, participants will undergo the relevant assessment and will also receive one dose of the study drug to ensure compliance.

The table below details each study time point and exactly what will occur. Each Action is explained in more detail below.

| **Visit** | **Drug** | **Action** | **Action** | **Action** | **Action** | **Action** | **Action** | **Action** | **Action** | **Action** |
| --- | --- | --- | --- | --- | --- | --- | --- | --- | --- | --- |
| 0 weeks | Washout |  |  |  |  |  |  |  | Bloods | Examination |
| 2 weeks | n |  | Microcirc |  |  |  |  |  |  | Examination |
| 1 month (4 weeks) | y | ECG | Microcirc | SF 36 | Urine | MRI/echo | 24hr BP | USS neck | Bloods | Examination |
| 2 month | y |  | Microcirc |  | Urine |  |  |  | Bloods | Examination |
| 3 months | y |  |  |  |  |  |  |  | Bloods | Examination |
| 4 months | y |  | Microcirc |  | Urine |  |  |  | Bloods | Examination |
| 5 months | y |  |  |  |  |  |  |  | Bloods | Examination |
| 6 months | y |  |  |  |  |  |  |  | Bloods | Examination |
| 7 months | n | ECG | Microcirc | SF 36 | Urine | MRI/echo | 24hr BP | USS neck | Bloods | Examination |

**Time** – 0 weeks refers to recruitment, consent and enrolment. Randomisation will occur at month 1 (4 weeks after recruitment). The study will end at month 7 after recruitment. Patients will receive the study drug for 6 months in total.

**Drug** – at month 1 (week 4) patients will be randomized to and receive at that visit either placebo or ergocalciferol. Patients will receive all 9 capsules of study medication at this time. They will be required to take 1 dose weekly at home in the first month. Further study medication will be taken at subsequent clinic visits and patients will be observed swallowing their medication either by pharmacy staff or an investigator.

**ECG** – a 12 lead cardiac ECG will be undertaken. This is a painless, non-invasive procedure.

Duration 5 minutes.

**Microcirc** – This process involves four assessments of the microcirculation and will take place at a clinic visit in the same room.

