1. Pulse wave velocity. An assessment of the speed of the pulse transmission in the major blood vessels of the body. Patients will have blood pressure cuffs placed around the thigh and neck. The cuff around the neck poses NO DANGER TO THE PATIENT AS IT ONLY INFLATES TO 60mm Hg – BELOW SYSTOLIC BLOOD PRESSURE. At worst, patients may feel a gentle pressure sensation around the neck. FULL RESUCITATION EQUIPMENT IS AVAILABLE ON SITE AND THE INVESTIGATORS AND CLINIC STAFF ARE TRAINED IN ADVANCED LIFE SUPPORT TECHNIQUES

Duration – 5 minutes

2. Iontophoresis. An assessment of skin microvascular function. Two compounds (AcH and SNip) are transmitted through the skin by the use of a very low electrical current into the small blood vessels located just under the skin. A laser Doppler probe records the response of the microvasculature. This is a non-invasive test and the drug dose is too low to cause any systemic absorption. Minor skin irritation has been reported but is usually mild and self limiting.

Duration - 15 minutes

3. Skin autofluorescence – An assessment of the build up of advanced glycation end products (AGE), which are a marker of oxidative stress. Patients place their arm over an ultraviolet light and results of AGE product accumulation are downloaded to a computer. This is a painless and non-invasive test.

Duration – 5 minutes.

Sublingual microvascular flow using sidestream darkfield (SDF) imaging – this is a non-invasive imaging tool to assess intra-vital capillary blood flow. A small camera (0.7cm) with a replaceable sterile cap is placed under the tongue in a similar way to temperature measurement with a mercury thermometer. 3 separate images are collected during one reading. These recordings will occur at visit 3, 6 and 9.

Duration – 5 minutes

**SF 36 –** Patients will be asked to fill in this standardized questionnaire about quality of life.

Duration - 10 minutes.

**Urine –** patients will be asked to give a clean catch urine specimen when they arrive at clinic which will be divided into 3 samples (urine sodium, urine calcium and urine PCR). Urine samples will be spun down so no cellular component will be retained or studied.

Duration – 5 minutes

**MRI –** Cardiac MRI scanning will take place at the London Chest Hospital and will be supervised by specialist medical and radiography staff. We will measure left ventricular mass and ejection fraction. The examination will not usually require contrast media to be injected.

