# 7. Statistical Plan

## Sample Size Determination

This study is powered to detect a difference in microcirculatory function as assessed by iontophoresis. It is likely that if a difference is seen in microcirculatory function as assessed by iontophoresis that the other microcirculatory assessments will follow the same trend

We expect 85% failure in the placebo group and 50% failure in the intervention arm (35% difference in success). We have set alpha=0.05 and beta=0.1 which gives us 90% power.

Therefore:

n=[((15x85)+(50x50))/35^2]x10.5=32 patients in each arm

In order to ensure we achieve a total of 32 patients in each arm for an adequately powered study, we will recruit 40 patients per arm to allow for withdrawals and protocol violations.

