## Statistical Methods

Full statistical support will be provided for data analysis. Differences between means will be analysed by student’s t test. Multiple regression analyses will be applied to determine which factors are associated with improved microvascular function. STATA software will be used for analysis. Baseline demographics will be recorded for all participants. The study design is in line with CONSORT guidelines.

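### Five co-equal primary measures share one alpha of 0.05 with no deciding measure, visit or success rule; if any one result counts, the false-positive chance can rise to about 18–23% at month 7

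*Combined protocol and SAP*

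**What the plan says.** Primary Study Endpoints has one numbered item, which covers "pulse wave velocity (PWV), iontophoresis of acetyl choline (AcH) and sodium nitroprusside (SNip), skin autofluoresence (AF) and side stream dark field imaging" of the sublingual circulation. It gives an expected direction for each technique but no ranking and no time point.

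Study Procedures and Schedule of Assessments describes the same package: "This process involves four assessments of the microcirculation and will take place at a clinic visit in the same room". Randomisation is at visit 3 (month 1). The microcirculatory assessments after that fall at visits 4, 6 and 9 (months 2, 4 and 7). For sidestream darkfield (SDF) imaging the text narrows this: "These recordings will occur at visit 3, 6 and 9".

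Sample Size Determination states "This study is powered to detect a difference in microcirculatory function as assessed by iontophoresis" and says it is likely "that the other microcirculatory assessments will follow the same trend". On error rates it says "We have set alpha=0.05 and beta=0.1 which gives us 90% power". Its inputs are binary: "We expect 85% failure in the placebo group and 50% failure in the intervention arm (35% difference in success").

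Statistical Methods says "Differences between means will be analysed by" Student's t test and adds multiple regression. It names no outcome, visit or adjustment. Appendix 1 keeps the microcirculatory assessments for the added arm, which it calls a pilot, and ends that arm at visit 6 (month 4).

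**The concern.** An alpha of 0.05 is a property of one test, or of a family of tests with a stated rule. Here the primary family has several members and no rule. Nothing says which measure decides, at which visit, how many must be positive, or how the error is shared. One nominally significant result could therefore be reported as meeting the primary objective, with the measure and visit settled after the data are seen. A mixed result, such as a better acetylcholine response with unchanged pulse wave velocity, would have no agreed reading. The expectation that the other measures will move with iontophoresis is a forecast and controls no error.

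By contrast, the secondary endpoint for kidney function does carry time points (0 and 6 months). None of the primary measures does.

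**Working it through.** **1. The plan's own sample size.** Inputs from Sample Size Determination: 85% v 50% failure, alpha 0.05, power 90%.

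- Multiplier: (1.960 + 1.282)² = 10.51, the plan's 10.5. So alpha is two-sided, although the text does not say so.
- n = [(15×85 + 50×50)/35²] × 10.5 = (3775/1225) × 10.5 = 32.4. The plan states 32 per arm and recruits 40.

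The figure reproduces. It is for one binary outcome tested once.

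**2. Count of comparisons.**

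- Final visit: pulse wave velocity, acetylcholine response, nitroprusside response, skin autofluorescence, SDF = 5. Counting iontophoresis once gives 4.
- All post-randomisation visits: four measures × 3 visits + SDF × 2 visits = 14.
- Appendix 1 arm (visits 4 and 6; SDF at visit 6 only): 4 × 2 + 1 = 9.

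**3. Chance of at least one p < 0.05 when the drug has no effect.** For k independent tests this is 1 − 0.95^k: two tests 9.8%, four 18.5%, five 22.6%. For correlated tests I simulated multivariate normal test statistics. The documents give no correlations, so these are assumptions.

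| Tests at month 7 | corr. 0 | corr. 0.3 | corr. 0.5 |
|---|---|---|---|
| 5 (all measures) | 22.6% | 20.9% | 18.3% |
| 4 (iontophoresis once) | 18.5% | 17.3% | 15.6% |
| 2 (iontophoresis only) | 9.8% | 9.5% | 9.1% |

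At a correlation of 0.9 the five tests still give 10.2%.

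| 14 tests, all visits | between-visit 0.5 | between-visit 0.8 |
|---|---|---|
| between-measure 0.2 | about 45% | 38% |
| between-measure 0.5 | 39% | 32% |

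Iontophoresis alone over three visits (six tests) gives 17–22% for between-measure correlation 0 to 0.5 and between-visit 0.6 to 0.8. The nine Appendix 1 comparisons give about 31% at between-measure 0.3 and between-visit 0.7.

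**4. Direction of benefit only.** The intended rate is 0.05/2 = 2.5%. Five independent tests give 1 − 0.975⁵ = 11.9%, falling to about 9% at correlation 0.5. Fourteen tests give about 16–24% over the grid above.

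**5. Price of keeping all five primary.** Bonferroni gives 0.05/5 = 0.01 per test. The plan's formula becomes (3775/1225) × (2.576 + 1.282)² = 45.9, so 46 per arm, above the 40 recruited. With 32 per arm at 0.01, the same unpooled formula gives z = 0.35/√[(0.1275 + 0.25)/32] − 2.576 = 0.65, a power of about 74%.

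**The case against.** The strongest reply is that the plan does have a lead measure: the trial is sized on iontophoresis, and the rest are expected to follow. This has weight. A reader might infer that the plan has no preferred measure at all, and the sample-size section does not support that. On the narrower reading the month-7 figure is about 9–10%, roughly half the five-test figure. But sizing a trial on a measure does not make it the only primary endpoint. The endpoint section still lists all of them, and two drugs, an unnamed visit and an undefined failure remain.

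A reader might also infer that 32–45% is the error rate the plan sets. The documents do not support this either. They schedule measurements at three visits but nowhere say that each will be tested. Since the endpoint section speaks of change after therapy, an end-of-treatment comparison is a natural, though unstated, reading. The 32–45% is what the plan leaves open.

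Third, every percentage needs a rule that any one significant result is success, and the plan states no such rule. That is fair and is carried as a condition. The plan does not exclude the rule or offer another.

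Finally, the Appendix 1 arm is called a pilot without a reliable power calculation, and its section restates no alpha. Its 31% shows that the gap carries over; it is not a breach of an error rate set for that arm.

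**Conclusion.** The point holds in conditional form. The plan states one alpha of 0.05 but does not define the test to which it applies, so it does not secure that error rate. Under an any-one-counts rule and the assumed correlations, the false-positive chance at month 7 runs from about 9–10% (iontophoresis only) to 18–23% (all five measures). That is about two to four and a half times the stated level. The upper figures over all visits are possible, not planned. The exact size is uncertain. The gap in deciding measure, visit, success rule and adjustment rests on no assumption, and it should be closed before unblinding, because a choice made afterwards would not be credible.

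**What to change.** In Primary Study Endpoints and the statistical plan, before unblinding:

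- Name one iontophoresis response at visit 9 (month 7) as the single primary endpoint, tested at two-sided 0.05. Acetylcholine is an example; no section favours either drug, so the sponsor should choose and justify one.
- Make the other iontophoresis response, pulse wave velocity, skin autofluorescence, SDF and all month 2 and month 4 results secondary.
- If formal claims on other measures are wanted, test them in a fixed sequence, or by Holm among themselves, only after the primary is significant. Holm across all five would be inconsistent with giving the primary the full 0.05: its first step is 0.01, with the power loss shown above.
- State whether the primary is the binary failure outcome of the sample-size section, with failure defined, or a mean compared by t test. Make the power statement match.
- For the Appendix 1 arm, name the same measure at visit 6 (month 4) as primary and treat the rest as exploratory.

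The cost is mainly wording. With the binary outcome, the plan's formula still gives 32 per arm. A reader might infer that no power is lost in any case, but the documents contain no power calculation for a difference in means, so one would have to be done. The other cost is that a positive result on another measure alone would no longer count as primary success.

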## Secondary Study Endpoints

**1. Quality of life** – we expect improved quality of life in the treatment group as measured by the SF 36 questionnaire.

**2.** A range of in vitro assessments to establish measures of oxidative stress and platelet activity will be conducted in a laboratory at the Royal London Hospital with an established protocol for these techniques.

**3. Left ventricular mass** – we expect reduced LV mass in the treatment group as measured by cardiac magnetic resonance imaging (MRI).

**4. Carotid artery intimal thickness** – we expect unchanged intimal thickness in the treatment group as assessed by ultrasound of the carotid arteries. This will imply that any enhancement to vascular function occurs as a result of changes to the function rather than structure of the conduit vessels.

**5. Blood pressure** – we expect blood pressure to reduce over the study duration in the treatment group as measured by 24 hour ambulatory blood pressure.

**6. Cardiac events** – we will record any cardiac events (myocardial infarction, stroke etc) that occur in either group

**7.** **Progression of kidney disease** – we expect the treatment group to progress slower as assessed by estimated glomerular filtration rate (eGFR) at 0 and 6 months

**8.** **Proteinuria** – we expect reduced proteinuria in the treatment group as assessed by urine protein:creatinine ratio (PCR)

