The scan lasts approximately 1 hour and will measure left ventricular ejection fraction and left ventricular mass

2. Carotid ultrasound: To be conducted at the Royal London Hospital using a specialist vascular probe and ultrasound machine. 2 readings of carotid intimal thickness will taken from the left and right carotid arteries at visit 3 and 9. Mean values will be recorded. A specialist vascular ultrasound and probe are available. The software has a specific protocol for measuring carotid intimal media thickness.

3. ECG: To be conducted at the Royal London Hospital. Patients will be placed at 45 degrees supine in the same environmental conditions mentioned previously. A standard 12 lead ECG will be recorded.

4. 24 hour BP: This will be conducted as an outpatient on a day to suit the patient. Formal reports will be reviewed and mean BP measures entered in the CRF.

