**Study endpoints**

Cardiac MRI’s, echocardiograms, ECG’s and carotid ultrasound measurements will not be undertaken since there is likely to be very little significant change in these parameters over a three month study duration. The main focus of this study is the microcirculatory assessments which remain unchanged.

The inclusion criteria will be amended to include patients with a vitamin D level of <70nmol/L

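### Unchanged carotid thickness is to be read as evidence of a functional mechanism, but the plan sets no criterion for unchanged and small-to-moderate structural effects could be missed

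*Combined protocol and SAP*

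**What the plan says.** Under Secondary Study Endpoints, item 4, the protocol predicts: "we expect unchanged intimal thickness in the treatment group as assessed by ultrasound of the carotid arteries". It then says how that result will be read: "This will imply that any enhancement to vascular function occurs as a result of changes to the function rather than structure", a statement the same sentence limits to the conduit vessels.

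The measurement is described under Attachments (Carotid ultrasound): "2 readings of carotid intimal thickness will taken from the left and right carotid arteries at visit 3 and 9", with mean values recorded. By the visit table in Study Procedures, visits 3 and 9 are month 1 (randomisation) and month 7, so the scans are six months apart.

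The analysis text is general. Statistical Methods says: "Differences between means will be analysed by student’s t test", and adds multiple regression for factors associated with better microvascular function. The Study Summary adds only that parametric or non-parametric tests will be chosen after a check of normality. Sample Size Determination says: "This study is powered to detect a difference in microcirculatory function as assessed by iontophoresis".

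Appendix 1 (Study endpoints) drops carotid ultrasound, along with cardiac MRI, echocardiography and ECG, from the additional arm because "there is likely to be very little significant change in these parameters over a three month study duration".

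**The concern.** The plan gives an expected null result a positive meaning: if thickness does not change, the mechanism is functional. That inference needs evidence that any structural change is smaller than some stated amount. A test of difference that fails to reject does not supply it, because the same result arises when a real change is too small for the trial to detect.

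Two features add to the problem. The prediction is worded for the treated arm alone. If thickness rose on placebo and stayed flat on ergocalciferol, that would be a structural effect of treatment, yet the sentence would label it functional. Measurement error is also uncharacterised: the healthy-volunteer reproducibility work (Subject Recruitment and Screening) covers iontophoresis, skin autofluorescence, side stream dark field imaging and pulse wave velocity, but not carotid ultrasound.

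At stake is a mechanistic conclusion in the trial report. The primary comparison is not affected.

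**Working it through.** **Inputs.** From Sample Size Determination: failure 85% on placebo and 50% on active, 32 evaluable and 40 recruited per arm, and "We have set alpha=0.05 and beta=0.1 which gives us 90% power". Allocation is 1:1 (Method for Assigning Subjects to Treatment Groups). Not given anywhere: an SD, a margin, a reproducibility figure or a baseline-to-follow-up correlation for carotid thickness. Results are therefore in SD units, and the correlation r is an assumption shown over a range. Sidedness of alpha is not stated. The plan's multiplier of 10.5 matches two-sided, since (1.960 + 1.282)² = 10.5, so two-sided is used.

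**The plan's own figure.** [(15 × 85) + (50 × 50)] / 35² × 10.5 = 3775 / 1225 × 10.5 = 32.4, given as 32 per arm; 32 / 0.8 = 40. It reproduces (33 if rounded up), but it concerns a binary iontophoresis outcome and says nothing about carotid thickness.

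**Precision for a difference in means.** The 95% CI half-width is t(0.975, 2n−2) × √(2/n), in SD of the analysed variable.
- n = 32: 1.999 × 0.250 = 0.50 SD
- n = 40: 1.991 × 0.2236 = 0.45 SD

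**Chance of missing a true difference d.** This is the probability that a noncentral t variable with 2n−2 degrees of freedom and noncentrality d√(n/2) falls inside the two-sided 5% critical values.

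| True difference | Noncentrality, n = 32 / 40 | Missed, n = 32 / 40 |
|---|---|---|
| 0.3 SD | 1.20 / 1.34 | 78% / 74% |
| 0.5 SD | 2.00 / 2.24 | 50% / 40% |
| 0.8 SD | 3.20 / 3.58 | 12% / 6% |

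**With baseline adjustment.** Adjusting visit 9 for visit 3 multiplies the cross-sectional SD by √(1 − r²), so a difference of 0.5 cross-sectional SD becomes 0.5 / √(1 − r²) in the units of the test. At r = 0.7 that is 0.5 / 0.714 = 0.70; at r = 0.8 it is 0.5 / 0.6 = 0.83. Equivalence power is the chance that the 90% CI lies wholly within ±0.5 cross-sectional SD when the true difference is zero (two one-sided t tests at 5%).

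| Assumed r | √(1 − r²) | Missed at 0.5 SD, n = 32 / 40 | Equivalence power at ±0.5 SD, n = 32 / 40 |
|---|---|---|---|
| 0 | 1.000 | 50% / 40% | 26% / 43% |
| 0.7 | 0.714 | 21% / 13% | 74% / 86% |
| 0.8 | 0.600 | 9% / 4% | 90% / 96% |
| 0.9 | 0.436 | under 1% | over 99% |

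Smaller effects remain hard to exclude. At r = 0.8, a 0.3 SD difference becomes 0.3 / 0.6 = 0.5 in test units, so it is missed as often as the unadjusted 0.5 SD case: 50% / 40%.

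**The case against.** The strongest reply is that the design holds more information than the unadjusted figures suggest. The scans are paired, and readings are duplicated on each side and averaged. If visits 3 and 9 correlate well, an adjusted analysis could rule out a difference of 0.5 SD with good power. This stands. A reader might infer that the trial cannot distinguish no structural change from a missed one; the documents do not support that, because it would be true only at low correlations that they neither state nor exclude. But the plan names no adjusted analysis and no margin, so this potential is unused.

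A reader might also infer that the sentence yields a functional conclusion almost whatever happens. It does not: even unadjusted, a 0.8 SD difference is missed only 12%/6% of the time. The protocol says imply rather than prove, limits the statement to conduit vessels, and nowhere says that unchanged means p > 0.05. The gap is that no criterion is stated at all.

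The Appendix 1 remark might be taken as the sponsor's admission that carotid thickness cannot move during the main study. It concerns three months, a cohort with vitamin D below 70 nmol/L and a six-capsule regimen. The same remark drops cardiac MRI, yet the main study expects left ventricular mass to fall over six months. Extending it to six months is an inference, and the point does not rest on it.

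Finally, this is one explanatory sentence on one of eight secondary endpoints, and it could be handled with care at reporting. That limits its importance, but a criterion chosen after unblinding would carry less weight.

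**Conclusion.** The point holds. The plan commits in advance to a mechanistic reading of a null carotid result without saying what counts as null, and names no analysis that could support it. Small-to-moderate structural effects could pass as unchanged: with 32/40 per arm and no adjustment, 0.5 SD is missed in 50%/40% of trials and 0.3 SD in 78%/74%.

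These figures assume a two-sided 5% t test and are in SD of the analysed variable. With adjustment they depend on r, which is undocumented. Whether 0.5 SD matters in mm cannot be judged without an SD. The consequence is confined to a secondary, explanatory claim, but the text should be changed because following it as written can produce an unsupported conclusion.

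**What to change.** Delete the inference sentence from Secondary Study Endpoints, item 4. In Statistical Methods, state that carotid thickness will be reported as the between-arm difference at visit 9 adjusted for visit 3, with its 95% CI, as a descriptive result.

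If the mechanistic statement is to be kept, set an equivalence margin in mm, with its reason, before unblinding. Allow a statement of no structural change of the conduit vessels only if the 90% CI for the adjusted between-arm difference lies wholly inside that margin. Give the assumed SD and correlation so that the power of this check can be judged.

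The cost is a sentence or two in the protocol and analysis plan, with no new patients, visits or scans. The sponsor may lose a secondary mechanistic claim.
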